### Planned statistical analyses

The effect of cognitive training will be analyzed by repeated measures (mixed between-within) analysis of variance (ANOVA) with groups (control group/intervention group) as the between-subject factor and assessment time (baseline and all follow-up assessments) as the within-subject factor for all cognitive tests and questionnaires, respectively. Assumptions for repeated measures ANOVA will be tested using the Levene test for variance-homogeneity and Mauchly’s test for sphericity. If sphericity is violated, alpha levels will be adjusted using the Greenhouse-Geisser correction. Normal distribution will be tested using the Shapiro-Wilk test. To control for the possibility of confounder variables that could affect the results, we will conduct additional repeated measures analysis of covariance (ANCOVA), which includes covariates such as preoperative cognitive values, age, sex, education, psychiatric scores (depression/anxiety), and perioperative variables such as duration of extracorporeal circulation, administration of anesthesia, and number and size of ischemic lesions.

Post hoc explorative between-subject comparisons will be analyzed using the *t* test for independent samples. In this case, we will compare the intervention group with the control group by calculating a change score in cognitive values (post-training score minus pre-training score). The change in cognitive values is the dependent variable, and the treatment group (cognitive training group/control group) is the independent variable.

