Within-subject comparisons will be analyzed using the paired *t* test. When the assumptions for parametric tests (normal distribution, variance-homogeneity between two groups) are not given, the variables will be analyzed using non-parametric variance techniques. In this case, between-group differences will be calculated using the Mann-Whitney U test, using change scores in cognitive values (post-training score minus pre-training score) and the Wilcoxon signed-rank test for within-group comparisons. Nominal variables will be analyzed by Pearson’s chi-squared test. Depending on the parametric level of the data, correlation with continuous variables will be calculated using Pearson product-moment correlation, Spearman rank correlation, or Kendall tau correlation. Effect size of the cognitive training will be calculated by the difference in the pretest-posttest measure between the intervention and control group, weighted by the pooled standard deviation of the pretest measurement, because this is the recommended choice for a pretest-posttest controlled design [38]. The criterion for statistical significance will be set at *p* < 0.05. In the case of multiple tests, we will control *p* values using the false discovery rate (FDR) correction method [39]. Since we expect dropout of some patients on follow-up assessments, all patients will be included in the intention-to-treat analysis, where missing data will be imputed by a multiple imputation method. To evaluate the impact of missing data, a complete case analysis will also be performed, followed by best-worst and worst-best case sensitivity analyses.

Another approach to identifying a training effect on cognition will be to compare the frequencies of POCD and POCI between the groups using Pearson’s chi-squared test. POCD will be defined as a decline from pre to post assessment of 1 standard deviation in at least two neuropsychological parameters as this is a widely used method [2]. Similarly, POCI will be defined as an improvement from pre to post assessment of 1 standard deviation in at least two neuropsychological parameters.

Interim analyses will be carried out during the study period to identify adverse events, an overwhelming effect, or the futility of the experimental arm. In this case, the study could be terminated prior to its completion. The decision will be made by the study team.

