### Power and sample size estimation

Cognitive training for patients undergoing heart surgery administered by de Tournay-Jette et al. (2012) [19] revealed medium-to-large effect sizes (*η*^2^ = 0.10–0.23). We have decided to use the smaller effect size (*η*^2^ = 0.10) for calculation so as not to underestimate the required sample size. Using this effect size, 37 patients per group are needed to obtain statistical power of 80% at a significance level of *p* = 0.05 (two-tailed). Based on previous cardiosurgical studies, we estimate a dropout rate of 20% between each of the four assessment time points. Thus, the number of study patients recruited at baseline assessment was fixed at 72 patients per group. For sample size and statistical power calculations, we used G*Power-3 analysis software.

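### Pre-tests on the trial data choose each cognitive test's group comparison, their scope is not fixed, and neither route adjusts for the preoperative score

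*Protocol article*

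**What the plan says.** All points are in the Protocol article, Methods, *Planned statistical analyses*, unless noted.

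- The main analysis of every cognitive test and questionnaire is a mixed ANOVA. Group is the between-subject factor, and assessment time, with baseline as one of its levels, is the within-subject factor.
- Levene and Mauchly tests check its assumptions, and "Normal distribution will be tested using the Shapiro-Wilk test".
- An additional repeated measures ANCOVA takes covariates that include the preoperative cognitive values. This is the only place where baseline is a covariate.
- Explorative group comparisons use a t test on the change score, and within-group comparisons use a paired t test.
- If normality or equal variance is not met, "the variables will be analyzed using non-parametric variance techniques". Between groups this means Mann-Whitney "using change scores in cognitive values (post-training score minus pre-training score"); within groups it means the Wilcoxon signed-rank test.
- For the intention-to-treat analysis, "missing data will be imputed by a multiple imputation method".
- *Primary outcome measure* defines the primary outcome as the training effect on all objectively measured functions at discharge from rehabilitation.

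**The concern.** The results of assumption tests on the trial's own data decide, test by test, how the groups are compared. The two routes answer different questions. The ANOVA tests a group-by-time difference in means over all visits. The fallback tests a rank shift in one pre-post change. If the fallback applies to the main analysis, a single primary outcome would be reported as a mixture of the two, and both kinds of p value would enter the same false discovery rate correction. The planned effect size, a mean difference in change over the pretest SD, would not match the rank test's p value.

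The rule also leaves room for choice after the data are seen. The article does not say whether Shapiro-Wilk is run on raw scores, change scores or residuals, at which visits, or which of the planned analyses the fallback replaces.

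Neither route uses the preoperative score as a covariate, although every patient is tested on the day before surgery. That is where power can be gained.

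**Working it through.** **1. The plan's own figure.** Inputs from *Power and sample size estimation*: η² = 0.10, "at a significance level of *p* = 0.05 (two-tailed"), and "37 patients per group are needed to obtain statistical power of 80" percent.

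- f = √(0.10/0.90) = 0.333, so d = 2f = 0.667 for two groups.
- A two-sample t test with d = 0.667 has power 79.7% at 36 per group and 80.8% at 37. The figure of 37 reproduces.
- Dropout: "we estimate a dropout rate of 20% between each of the four assessment time points". Retention over three intervals is 0.8³ = 0.512, and 37/0.512 = 72.3, stated as 72.
- Expected at discharge: 72 × 0.8 = 57.6, taken as 57 per arm. At 12 months: 72 × 0.512 = 36.9, about 37.

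The sample size is not in question here.

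**2. What the default route adjusts for.** With two visits, the group-by-time F equals the square of the t statistic on the change score. The default and the fallback therefore both compare raw changes. The t test on change stands in for the ANOVA below. The power of the four-visit omnibus interaction was not computed.

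**3. Exact calculation, normal scores.** Assumptions (not in the article): pre-post correlation ρ = 0.6 and effect 0.5 SD.

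- Change score: variance 2(1 − ρ) = 0.80, standardised effect 0.5/√0.80 = 0.559.
- ANCOVA: residual variance 1 − ρ² = 0.64, standardised effect 0.5/√0.64 = 0.625.
- Noncentrality = effect × √(n/2).
  - n = 57: 2.98 and 3.34, giving power 84.1% (change) and 91.1% (ANCOVA).
  - n = 37: 2.40 and 2.69, giving 66.0% and 75.5%.

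No pre-test enters this calculation, so the gap of 7 to 10 points is due to the change score alone.

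**4. Simulation, same ρ and effect, 4,000 trials per row.** Skewed scores are log-normal with an assumed log-SD of 0.3 or 0.4. The route shown applies Shapiro-Wilk to raw scores in each arm and visit and Levene to the change, then uses Mann-Whitney on change if any test rejects and the t test on change otherwise.

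| n per arm | Scores | Fallback fires, raw / change tested | t on change | Pre-test route | ANCOVA raw | ANCOVA log |
|---|---|---|---|---|---|---|
| 57 | normal | 22% / 14% | 83.7% | 83.2% | 90.4% | – |
| 57 | log-SD 0.3 | 97% / 42% | 78.0% | 77.6% | 89.4% | 91.3% |
| 57 | log-SD 0.4 | 100% / 64% | 74.6% | 76.3% | 88.4% | 91.3% |
| 37 | normal | 22% / 14% | 65.9% | 65.0% | 75.0% | – |
| 37 | log-SD 0.3 | 89% / 34% | 59.2% | 58.8% | 73.0% | 75.4% |
| 37 | log-SD 0.4 | 98% / 50% | 56.4% | 57.0% | 70.7% | 74.6% |

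Other runs of these scenarios differ by a point or two. The rounded ranges are 74-84% against 87-91% at 57 per arm, and 55-66% against 69-76% at 37. The pre-test route stays within about 2 points of the t test on change throughout.

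**5. With the plan's own effect size.** Taking d = 0.667 on the log-change scale, log-SD 0.3-0.5 and ρ 0.5-0.7 (3,000 trials per scenario):

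- 37 per arm: t on change 65-74%, Mann-Whitney on change 69-74%, raw ANCOVA 80-88%, log ANCOVA 86-91%.
- 57 per arm: 84-90%, 87-90% and, for log ANCOVA, 97-98%.

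**6. Type I error.** Under the null (log-SD 0.4, ρ = 0.6), the two-stage procedure rejects in 5.4-5.7% of trials, and single methods in the same runs in 5.3-5.9%.

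**The case against.** Several stronger readings are tempting, and the article does not support them.

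- **That the fallback throws away baseline adjustment.** A reader might infer this from the move to raw change scores. But in the main ANOVA baseline is a level of the time factor, not a covariate, so there is none to lose. The text does not say that the additional ANCOVA is withdrawn.
- **That tests sent to the fallback lose power because of it.** Against the plan's own change-score comparison they do not. With stronger skew, Mann-Whitney is slightly better. Removing the pre-tests and keeping the planned ANOVA would recover almost nothing.
- **That skewed timed tests almost always reach the fallback.** This holds only if raw scores are tested (97-100% at 57 per arm); if change scores are tested it is about 40-65%. The article gives no distribution for any test, so the skewness is an assumption.
- **That the two-stage procedure inflates false positives.** None was seen.

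The scope can also be read narrowly. The fallback sentence follows the explorative t test and the paired t test, and its two replacements mirror them one for one. It may concern only those tests. Against that, the wording refers to variance techniques and to the same assumptions that are checked for the ANOVA. The ambiguity is itself part of the point.

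Finally, the log-normal scenarios suit a log-scale ANCOVA by construction. That is fair, but the raw-scale ANCOVA already recovers most of the gain. How to pool a U test over imputations is a detail that an analysis plan may settle, so it supports the fix but is not a separate fault.

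**Conclusion.** The point holds in a limited form. The between-group method is selected by pre-tests on the trial data, and neither the scale tested nor the analysis replaced is fixed. The primary outcome could therefore combine two kinds of comparison. This is a matter of clarity and pre-specification; no error-rate problem was found.

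The measurable loss comes from comparing unadjusted changes on either route. It is about 7 points for normal scores and up to about 17 for skewed scores at 57 per arm, and about 9 to 18 points at 37. These sizes rest on an assumed correlation of 0.6, an assumed effect of 0.5 SD, log-normal skew for the larger values, and analysis of observed patients only. With the plan's own effect size the loss is of the same order at 37 per arm and smaller at 57, where power is already high. The change is worth making, but the trial is not invalid without it.

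**What to change.** - Remove the Shapiro-Wilk and Levene results as a rule for choosing the analysis. Judge model fit from residuals.
- Make ANCOVA of the discharge score on group and preoperative score the single primary model for every cognitive test. Name in advance any transformation of timed tests (for example the log), and use robust or bootstrap standard errors.
- Pool the group coefficient over the planned imputations by Rubin's rules.
- Keep Mann-Whitney on change scores as a labelled sensitivity analysis, and state that it does not replace the primary model.

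This costs analysis wording only. It needs no further patients or assessments, because the preoperative score is already collected. The small downside is that effects on log-transformed tests are reported as ratios and are not in the original units.

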### Primary outcome measure

The primary outcome measure will be the training effect on all objectively measured neuropsychological functions at discharge from rehabilitation.

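### At the dropout the plan expects at 3 and 12 months, best-worst and worst-best filling of continuous scores will rarely be informative; a graded missing-data analysis should be added

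*Protocol article*

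**What the plan says.** In the protocol article, the section Planned statistical analyses sets an intention-to-treat analysis in which "missing data will be imputed by a multiple imputation method". To judge the impact of missing data it names two further steps: an analysis of complete cases, "followed by best-worst and worst-best case sensitivity analyses". The article does not say which values count as best or worst, and it attaches no decision rule to these analyses.

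The outcomes are mainly continuous: all cognitive tests and questionnaires, analysed by repeated measures ANOVA over baseline and all follow-ups, with change scores for post hoc comparisons. The same section also plans a comparison of the frequencies of POCD and POCI, which are binary.

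Power and sample size estimation says that "we estimate a dropout rate of 20% between each of the four assessment time points". The primary outcome is the "training effect on all objectively measured neuropsychological functions at discharge from rehabilitation", which is the first assessment after baseline.

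**The concern.** Best-worst filling gives every missing patient in the training arm a good value and every missing control patient a bad one; worst-best does the reverse. The distance between the two results grows with the share of missing values. With a large share it can exceed any plausible treatment effect, and the pair then says little about whether the result is robust.

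This matters because the extreme cases are the only check named that departs from the assumption that, given the observed data, dropouts resemble those who stay. Complete cases need a similar assumption. There is reason to probe it. Inclusion and exclusion criteria allows patients to stop because of worsening health, low motivation or not wishing to continue the training. The first two may be related to cognition, and the last can arise in one arm only. A reader will want to know how different the dropouts would have to be before the conclusion changes, and two extreme points do not answer that.

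**Working it through.** **Inputs from the article.** Eta squared 0.10 for the design and 0.23 as the top of the cited range; two-sided 0.05; 80% power; 20% dropout per interval over three intervals; 72 per group at baseline.

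**Inputs assumed here.** The score analysed has SD 1, dropout is equal in the two arms, and best and worst values are the arm mean plus or minus k SD, with k = 1 or 2. The article gives no fill values.

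**The plan's own figures.**
- f = sqrt(0.10/0.90) = 0.333, so d = 2 × 0.333 = 0.667.
- A two-sample t test then needs 36.3, rounded up to 37 per group (power at 37 is 0.808). This agrees with "37 patients per group are needed to obtain statistical power of 80% at a significance level of" 0.05.
- 37/0.8³ = 72.3, and 72 × 0.512 = 36.9. The 72 per group is reproduced, which confirms that the plan compounds 20% over three intervals.

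**Missing share m.**
- Discharge: 1 - 0.8 = 0.20.
- 3 months: 1 - 0.8² = 0.36.
- 12 months: 1 - 0.8³ = 0.488.

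**Shift of the group difference.** Each arm mean moves by k × m in opposite directions, so the shift is 2km. The worst-best difference at the design effect is 0.667 - 2km.

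| Visit | m | Shift, k = 1 | Worst-best, k = 1 | Shift, k = 2 | Worst-best, k = 2 |
|---|---|---|---|---|---|
| Discharge | 0.20 | 0.40 | +0.27 | 0.80 | -0.13 |
| 3 months | 0.36 | 0.72 | -0.05 | 1.44 | -0.77 |
| 12 months | 0.488 | 0.98 | -0.31 | 1.95 | -1.28 |

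**Observed effect needed to survive worst-best.** After filling, the variance within an arm is (1 - m)(1 + mk²). With 72 per arm, worst-best stays significantly positive only if the observed d exceeds 2km + 1.977 × sqrt(2/72) × sqrt[(1 - m)(1 + mk²)].
- Discharge: 0.40 + 0.32 = 0.72 (k = 1); 0.80 + 0.40 = 1.20 (k = 2).
- 3 months: 0.72 + 0.31 = 1.03 (k = 1); 1.44 + 0.41 = 1.85 (k = 2).
- 12 months: 0.976 + 0.288 = 1.26 (k = 1); 1.952 + 0.405 = 2.36 (k = 2).

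Eta squared 0.23 corresponds to d = 2 × sqrt(0.23/0.77) = 1.09. Even that effect falls short of the 12-month thresholds.

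**Simulation.** 1,500 trials per setting, normal scores, 72 per arm, missingness unrelated to outcome, unadjusted p < 0.05. A third rule fills with the pooled observed minimum and maximum. The table shows the design effect, d = 0.667; rules are in the order 1 SD / 2 SD / min-max.

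| Visit | Worst-best still significantly positive | Two scenarios significant in opposite directions |
|---|---|---|
| Discharge | 43% / 0.5% / 0% | 0.1% / 6% / 54% |
| 3 months | 5% / 0% / 0% | 11% / 94% / 100% |
| 12 months | 0.9% / 0% / 0% | 52% / 100% / 100% |

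At 3 and 12 months the two scenarios differed in significance or direction in at least 95% of trials under every rule. At d = 1.09 with the mildest rule, worst-best stayed positive in 98% of trials at discharge, 61% at 3 months and 27% at 12 months. The planned false discovery rate correction was not applied; it could only make survival harder.

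**The case against.** A reader might infer that the two scenarios contradict each other almost whatever the data show, the primary outcome included. The figures do not support that. At discharge with 1 SD filling, both scenarios favour training at the design effect, opposite significant results are nearly absent (0.1%), and worst-best survives in 43% of trials, or 98% at eta squared 0.23. Under that rule the check can support a primary result.

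The size of the effect also depends on fill values the article does not give. A condensed article may leave these to the full protocol or analysis plan, so their absence is not a finding. This stands for discharge, where the reading changes with the rule. It does not rescue the later visits, where at the design effect every rule tried gave the same answer.

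A reader might add that some tests are timed and have no natural worst value. The descriptions under Neuropsychological assessment do not establish this, and the point does not need it.

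Extreme cases are meant as outer bounds, multiple imputation remains the main analysis, and nothing says that failing a bound overturns a result. That is correct, and it keeps the matter minor. But a bound that most plausible results fail tells the reader little.

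Finally, dropout is counted from the assessment before surgery, while Fig. 1 places allocation after transfer to rehabilitation, so some early losses may precede allocation. The 20% at discharge is thus an upper figure for losses by arm. If all first-interval losses came before allocation, the shares among allocated patients would be 0%, 20% and 36%. The 12-month shift would still be 0.72 SD with 1 SD filling, above the design effect, but the 3-month visit would then behave like the discharge row. Against this, the plan counts 72 per group at baseline, which favours the shares used here.

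**Conclusion.** The point holds for continuous scores at 3 and 12 months. With 36% and about 49% missing, even 1 SD filling moves the difference by 0.72 and 0.98 SD against a design effect of 0.667 SD. At that effect, worst-best stayed significantly positive in at most 5% and 0.9% of simulated trials. At discharge, with up to 20% missing, the value of the check depends on the fill rule (+0.27 SD with 1 SD, -0.13 SD with 2 SD); the documents do not support calling it uninformative there.

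The conclusion assumes that dropout runs as planned and equally in both arms, that the design effect applies at the later visits, and that filling is at least as extreme as 1 SD. Lower dropout or a much larger effect would make the bounds more useful. The main analysis and the sample size are not affected. This is a worthwhile improvement to the sensitivity analysis, no more.

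**What to change.** For the continuous scores, add a delta-adjusted analysis built on the multiple imputation already planned:

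- Shift the imputed values in the training arm in the unfavourable direction for each score, in steps from 0 to a prespecified limit, for example 0 to 0.5 SD. The limit is an assumption and must be justified. The pooled pretest SD, which the plan already uses for its effect size, is a natural unit.
- Repeat with the shift applied in both arms. With equal dropout a common shift largely cancels, so this version mainly shows the consequence of unequal dropout.
- Report, for each conclusion, the shift at which it changes, or state that it does not change within the range.

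A training-arm shift of 0.5 SD moves the difference by m × 0.5, that is 0.10, 0.18 and 0.24 SD at the three visits, so the result can be read in steps.

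The best-worst and worst-best cases may stay as outer bounds and for the binary POCD and POCI outcomes, but should not be the only analysis that departs from missing at random. The cost is some extra programming and agreement on the delta range before the data are seen; no new data are needed.

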## Methods

### Study design and enrollment

This study is a multicenter, randomized controlled trial conducted at the department of cardiac surgery of the Kerckhoff Heart and Thorax Center in Bad Nauheim, Germany, and at the department of cardiovascular surgery of the University Hospital Giessen, Germany. It complies with the Declaration of Helsinki and has been approved by the ethics committee of the Justus Liebig University Giessen (ref. 28/14). The study coordinator receives information about planned elective cardiac surgery from the participating study centers, which he screens according to eligibility criteria. Potential patients will be contacted and informed verbally and in writing in detail about the purpose, procedure, and possible consequences of the study project. If the patient agrees to participate, a written informed consent form will be signed by the patient and the investigator prior to the patient’s enrollment.

Our study team consists of members of the departments of neurology, neuropsychology, neuroradiology, heart surgery, and rehabilitation who are responsible for running the study, including preparing the protocol, monitoring the study and writing the study reports. The study protocol follows the SPIRIT (Standard Protocol Items: Recommendations for Interventional Trials) guideline (see Additional file 1).

Due to the planned small sample size, the expected lack of harm and the relatively short execution time of the cognitive training (3 weeks), the implementation of a data monitoring committee was not considered.

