### Blinding

Surgeons, radiologists and neuropsychologists who are involved in the outcome variables will be blinded to the randomization status. Cognitive testing and training will be carried out by two different, experienced neuropsychologists in order to maintain the blinding. During follow-up assessments, patients may tell the blinded neuropsychologist accidentally before the start of the neuropsychological test whether or not they have received previous cognitive training. In this case, however, the neuropsychological test will be performed and discussed in the study reports.

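### Interim looks that can stop the trial for efficacy are left to the study team's discretion with no stated boundary, so 5% type I error is not assured and assessor blinding is unprotected

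*Protocol article*

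**What the plan says.** Four statements in the Protocol article bear on this point.

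- **Interim looks and their purpose** (Planned statistical analyses): "Interim analyses will be carried out during the study period to identify adverse events, an overwhelming effect, or the futility of the experimental arm". The consequence follows: "In this case, the study could be terminated prior to its completion". On who decides: "The decision will be made by the study team".
- **Error control** (same section): "The criterion for statistical significance will be set at" p < 0.05. Where there are multiple tests, the plan will control p "values using the false discovery rate (FDR) correction method". No other adjustment is named.
- **Oversight** (Study design and enrollment): citing the small sample, the expected lack of harm and the short training period, the article says that "the implementation of a data monitoring committee was not considered". It also says: "Our study team consists of members of the departments of neurology, neuropsychology, neuroradiology, heart surgery, and rehabilitation". That team runs and monitors the study.
- **Blinding** (Blinding): "Surgeons, radiologists and neuropsychologists who are involved in the outcome variables will be blinded to the randomization status". The safeguard given is that testing and training are done by different neuropsychologists.

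**The concern.** A look that can stop a trial for benefit is a second chance to declare success. Unless its threshold is strict or the final level is lowered, the chance of a false positive over the whole trial exceeds the nominal level. Here the text commits to such looks and allows them to end the trial. It leaves the decision to the investigators' judgement and keeps 0.05 as the only stated criterion. The false discovery rate method deals with many outcomes tested at one time. It does not deal with the same outcome tested several times as data accrue. A trial stopped early on a favourable result also tends to overstate the effect.

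The second issue is who sees the results. A judgement on benefit or futility ordinarily needs results by arm. Patients know whether they trained and the control group has no placebo, so blinding of the examiner is the main protection for these examiner-administered tests. The article does not say that outcome assessors are kept away from interim comparisons.

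**Working it through.** **1. Was anything reserved for interim testing?** Inputs from Power and sample size estimation: η² = 0.10, 80% power, two-tailed 0.05, 37 per group, 20% dropout between successive assessments (three intervals), 72 per group recruited.

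- f = √(0.10 / 0.90) = 0.333, so d = 2f = 0.667.
- Two-sided two-sample t test (noncentral t): n = 36 gives 79.7% power and n = 37 gives 80.8%. The stated 37 is reproduced.
- Dropout: 37 / 0.8³ = 37 / 0.512 = 72.3. Conversely 72 × 0.512 = 36.9 remain. The stated 72 is reproduced to within rounding.

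The sample size is therefore that of a single analysis at the full 0.05, with nothing set aside for interim looks.

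**2. What would repeated looks do to the error?** The article gives neither the number of looks nor the threshold, so both are assumptions. For one endpoint and K equally spaced looks (the final one included), the test statistics under the null are multivariate normal with correlation √(tᵢ/tⱼ) for information fractions tᵢ ≤ tⱼ. The overall two-sided error is

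1 − P(|Z₁| < c₁, …, |Z_K| < c_K).

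Two cases bracket the plausible range: every look at p < 0.05 (c = 1.96 throughout), or interim looks at p < 0.001 (c = 3.29) with the final test at 0.05.

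| Total looks | Every look at 0.05 | Interim at 0.001, final at 0.05 |
|---|---|---|
| 1 | 5.0% | 5.0% |
| 2 | 8.3% | 5.02% |
| 3 | 10.7% | 5.05% |
| 4 | 12.6% | 5.08% |
| 5 | 14.2% | 5.11% |

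A simulation of 1,000,000 null trials gives the same figures for the 0.05 column (0.083, 0.107, 0.126 and 0.142 for two to five looks).

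To hold 5% exactly with two looks, a Pocock rule would need 0.0294 at each. An O'Brien-Fleming rule would need 0.0052 and then 0.0480.

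**3. Who decides, and who must be blind?** The disciplines can be set side by side.

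| Discipline in the study team | Role to be blinded |
|---|---|
| Heart surgery | Surgeons |
| Neuroradiology | Radiologists |
| Neuropsychology | Neuropsychologists involved in the outcomes |
| Neurology, rehabilitation | none named |

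Three of the five disciplines in the deciding group are also disciplines with a blinded role. The separate tester and trainer stop the tester learning a patient's allocation by delivering the training. They do nothing about interim results by arm.

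**The case against.** **The threshold is not stated, so inflation is not shown.** The article nowhere says that an interim look uses 0.05, and the word overwhelming suggests a stricter bar. With p < 0.001 the excess over 5% is negligible, and safety or futility looks alone add none. This stands. A reader might infer that the stated 5% is simply false, but the document does not support that. It supports only that 5% is not secured, because overwhelming is undefined and the decision is discretionary.

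**Boundaries and timing often sit in the analysis plan or full protocol.** True, and neither is shown, so the accurate wording is that no adjustment is stated, not that none exists. The allocation of the decision is different. The article itself gives it to the study team and explains why there is no committee, so that choice is made here.

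**The blinding breach is inferred.** A reader might conclude that the assessors are unblinded. The article lists departments, not individuals. It does not say that the testing neuropsychologist belongs to the deciding group or sees results by arm. Group-level results also do not reveal one patient's allocation. This stands too: the text lacks a firewall but does not record a breach. The risk remains real, because the Blinding section itself expects that some patients may disclose their allocation at follow-up. An assessor who also knew the interim trend would then be doubly exposed.

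**The calculation is for one endpoint.** The primary outcome covers all objectively measured neuropsychological functions. The figures therefore illustrate the effect of repeated looks and are not the error rate of the full primary analysis. An interim rule also needs an outcome to be named for it.

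**Conclusion.** The point holds in a conditional form. The article provides for stopping on efficacy at the investigators' discretion, without a committee or a stated boundary. Its one criterion and one correction do not cover repeated looks, and its sample size assumes a single analysis at full alpha. Following that text does not assure 5% type I error. For one endpoint and equally spaced looks, the overall error lies between about 5.0% (interim threshold 0.001) and 8.3%, 10.7% or 14.2% (two, three or five looks, all at 0.05). Where it falls depends on a number of looks and a threshold that the article does not give.

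Assessor blinding is unprotected against interim results by arm, because the deciding and blinded disciplines overlap and no separation is stated. That is a gap in safeguards, not evidence that blinding has failed.

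**What to change.** Preferred: delete the efficacy and futility looks and keep only a review of adverse events pooled over both arms. The final test at 0.05 then needs no adjustment for interim looks.

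If an efficacy look is to stay, state all of the following in advance:

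- one look, at a fixed time, on one named outcome;
- stop for benefit only at p < 0.001, with the final test at about 0.05 (5.02% overall, from the table);
- futility as non-binding guidance;
- results by arm seen only by a person not involved in outcome assessment or recruitment, who returns only continue or stop.

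In either case, report any looks already taken: when, on which data, who saw them and what was decided. Recruitment began in July 2016 and the cited protocol version dates from 2019, so new wording alone would not undo earlier looks.

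The cost is about a paragraph of text, plus naming an outcome and an independent person if the look is kept. The small downside is losing an informal option to stop early.
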